## Abstract

Background: Chronic and noncommunicable diseases, including cancer, are a significant global public health concern. Family members or friends who serve as caregivers significantly contribute to supporting cancer patients without formal medical training. In most cases in Bangladesh, women perform caregiving activities with household responsibilities and lack adequate support from the family and healthcare systems; consequently, they face a significant burden as caregivers. This study aims to assess the effectiveness of combined mobile health (mHealth) psychoeducation and the Benson relaxation technique (BRT) on the caregiving burden among female informal caregivers of cancer patients in Bangladesh.

Methods: We shall conduct a prospective, open-label, two-arm (1:1), randomized controlled trial in a hospital, focusing on the burden of informal female caregivers of cancer patients in Bangladesh. The combined intervention will be delivered to the intervention group through mHealth starting April 2024 and will span six months. Participants' data will be collected through face-to-face interviews using the Zarit Burden Interview (ZBI), the Hospital Anxiety Depression Scale, and the World Health Organization Quality of Life Bangla Short Instrument. Outcomes will be assessed at the baseline, midline, and endline. We shall employ descriptive statistics such as frequencies, percentages, means, and standard deviations. The t-test or Mann-Whitney U test will be used to compare continuous variables. Additionally, a two-way repeated-measures analysis of variance will be employed to evaluate the outcomes.

Results: Participant enrollment began in January 2024, and recruitment is ongoing. The results of this study will be disseminated through publications and conferences. No external professional writers were involved in writing this manuscript.

Conclusion: This study addresses the gap in the assessment of combined interventions for caregiver burden in Bangladesh. These outcomes may provide valuable insights into caregivers' well-being, caregiving responsibilities, and the potential for integrated interventions to reduce the burden, especially among women. If effective, we recommend the national integration of psychoeducation and BRT using mHealth.

## Introduction

Chronic and noncommunicable diseases represent major challenges of the 21st century, which ultimately result in severe consequences and societal issues for patients and communities worldwide [1]. Cancer, which claims the lives of more than 9.6 million people annually, 70% of whom are from lower- and middle-income countries, is a significant public health concern worldwide [2]. Cancer significantly affects patients, their families, and caregivers. In most cases, family members or close friends play a crucial role as informal caregivers in supporting and assisting cancer patients; these caregivers usually have no knowledgeable medical training [3]. The role of these caregivers is crucial throughout the disease trajectory of patients with cancer, that is, from diagnosis to the final stages of the illness. In the context of cancer, caregivers commonly face significant challenges related to patient treatment, symptom management, and the fulfillment of daily care needs. Consequently, it usually increases the levels of caregiving burden, anxiety, and depression and reduces the quality of life (QOL) that caregivers encounter throughout their caregiving journey [4,5].

The prevalence of caregiving burden among caregivers of cancer patients is significant and well-established. A study in India found that 92.5% of caregivers experienced mild-to-severe levels of burden [6]. Furthermore, a systematic review of various studies published on cancer nursing indicated that between 37% and 100% of family caregivers reported experiencing a certain level of burden [7]. Caregiving burden is negatively correlated with depression and anxiety [8]. Another systematic review highlighted that the prevalence of depression and anxiety among cancer caregivers was 42% and 47%, respectively [9]. The same study indicated that nearly half of the caregivers experienced severe levels of depression (46%) and anxiety (53%). Additionally, caregiving demands can result in physical, emotional, and social limitations, resulting in reduced overall QOL [10]. A previous study reported that the caregiving burden negatively impacts the QOL of caregivers of cancer patients [11].

Over the past few years, there has been a growing interest in utilizing digital health technologies, particularly mobile health (mHealth). As defined by the World Health Organization (WHO), "mHealth is a term used for medical and public health practices supported by mobile devices such as mobile phones, patient monitoring devices, personal digital assistants (PDAs), and other wireless devices" [12]. mHealth involves various communication channels such as short messaging services (SMS), phone calls, online platforms, social networks, and emails to provide interventions. mHealth psychoeducational interventions can equip caregivers with accessible information, self-care tools, and resources specific to their caregiving journey, which can improve their knowledge, skills, and self-efficacy, and ultimately enhance their capacity to manage caregiving responsibilities and their well-being [13,14]. One study reported the effectiveness of mHealth psychological interventions as a viable treatment approach for caregivers who experience high levels of stress or burden [15]. Relaxation techniques are nonpharmacological methods used to relieve mental health problems among patients and their caregivers. Among the various relaxation techniques available, the Benson relaxation technique (BRT) is considered one of the most effective, low-cost, and straightforward methods of intervention [16]. These techniques include mindfulness exercises that specifically treat a variety of mental and emotional symptoms such as burden, anxiety, pain, depression, mood swings, and self-esteem. Related studies have demonstrated that BRT is more effective in reducing caregiving burden, anxiety, and depression in various populations, including among caregivers [17,18].

In Bangladesh, there are 1.3-1.5 million cancer patients, among 0.2 million newly diagnosed patients every year [19]. Most female caregivers play a vital role in personally supporting patients. As a cultural expectation, women are generally expected to perform caregiving activities while maintaining household responsibilities and familial commitments, which places an additional burden on them. Females in Bangladesh experience the greatest disadvantages and vulnerabilities for numerous reasons. Research shows that compared with their male counterparts, female caregivers experience higher levels of burden and emotional distress, which significantly affects their QOL [10,11]. However, the unique cultural context, gender inequalities, and social norms in Bangladesh may cause additional difficulties for female caregivers. Therefore, it is essential to create effective interventions and support systems to alleviate their burden and improve their mental health and overall QOL. To the best of our knowledge, although there is growing evidence supporting the effectiveness of BRT and mHealth psychoeducational interventions separately, there is a significant knowledge gap, and their combined impact on informal female caregivers of cancer patients remains relatively unexplored. This research protocol following the PICOT (Population, Intervention, Comparison, Outcome, Time) framework outlines a randomized controlled trial aimed at evaluating the effectiveness of integrating an mHealth psychoeducational intervention and BRT in reducing the negative effects of the burden of caring for cancer patients in Bangladesh. This structured framework addresses specific research questions as follows: In female informal caregivers of cancer patients in rural Bangladesh (population), the combined mHealth psychoeducational intervention and Benson relaxation technique (intervention), compared with standard care (comparison), result in a reduction in caregiver burden, anxiety, and depression and an improvement in QOL (outcome) over a six-month period (time).

The results of this study suggest that the integration of mHealth psychoeducation and BRT is effective in reducing caregiver burden, increasing psychological well-being, and improving overall QOL.

## Materials and methods

Design and study site

This study is a hospital-based, single-centered, prospective, open-label, two-arm (1:1), randomized controlled trial involving the burden experienced by the caregivers of cancer patients and will be conducted in the rural areas of Bangladesh. This research is structured following the Consolidated Standards of Reporting Trials (CONSORT) and adheres to the SPIRIT (Standard Protocol Items: Recommendations for Interventional Trials) guidelines [20,21]. The intervention is scheduled to begin in April 2024, with the entire study spanning six months. Figure 1 shows a flowchart of the study. This study will be conducted at the Khwaja Yunus Ali Medical College and Hospital, located in Enayetpur, Sirajganj, Bangladesh. This hospital is recognized as a specialized cancer center in the northwestern part of the country. The study site has been selected purposefully because of the convenience of the research objectives.

**Figure 1 FIG1:**
[figure not shown]
Flowchart of the study

Study participants

Eligibility Criteria

Initially, a baseline study was conducted to assess the caregiving burden among female informal caregivers of cancer patients. Subsequently, in this study, individual caregivers are enrolled based on their experiences with mild-to-moderate, moderate-to-severe, and severe burdens, as determined using the Bangla version of the Zarit Burden Interview (ZBI)-22 [22]. The inclusion criteria were as follows: females aged 18 years or older and those who have been providing care to a cancer-diagnosed patient for at least six months. The exclusion criteria included those who refused to collaborate with the ongoing study, caregivers receiving financial compensation or employed as formal caregivers, those experiencing extremely traumatic events that occurred during the study (such as the deaths of loved ones or patients, separations, etc.), caregivers undergoing psychotropic drug treatment, and those without smart mobile devices at home.

Sample Size

We used the G*Power software (Version 3.1.9.7) to calculate the sample size. An effect size of 0.72 was estimated based on a similar previous study that examined the caregiving burden among family caregivers [23]. The sample size required for the study was 84 caregivers, based on a power analysis of the difference between two independent means (two groups), a confidence level of 0.95, and a statistical power of 0.90. Eighteen additional caregivers will be recruited to compensate for potential dropouts. Following a 20% dropout rate, the total number of participants was 102, 51 in the intervention group (IG) and 51 in the control group (CG).

Data Collection and Follow-Up

Data will be collected at baseline (before the intervention), midline (after three months of intervention), and endline (after six months of intervention), through face-to-face interviews with participants. Sociodemographic data will be collected from two categories: caregivers and patients. Patients' basic characteristics such as sex, age, education, and marital status will be obtained directly from the patients. Additionally, relevant cancer-related information including cancer stage, type of cancer, duration of cancer, medical or other types of insurance coverage, and treatment type will be collected from hospital records. Data on caregivers' sociodemographic characteristics includes age, marital status, education level, employment status, monthly family income, presence of chronic diseases, relationship with the patient, duration of caregiving (months), and daily caregiving time (hours). Moreover, the ZBI-22 [22], Hospital Anxiety Depression Scale (HADS) [24], and World Health Organization Quality of Life Instrument (WHOQOL-BREF) [25] will be used to assess the level of burden, anxiety, depression, and QOL, respectively, all of which were validated and adopted in the local language, Bengali.

Randomization

After computer-generated stratification, participants will be randomly assigned according to their degree of burden, anxiety, and depression. In this study, there will be a 1:1 open-label randomization for either the IG or the CG. Randomization will be performed by a trained research assistant not involved in the intervention. The researchers will start organizing the study as soon as the research assistant informs them which participants are assigned to the IG or CG.

Intervention

In the IG, we designed a combined intervention using self-determination theory (SDT) and the BRT, which were used separately in previous studies, and successfully reduced the severity of the caregiving burden among caregivers [17,26]. There will be six sessions over six months, where each session will be conducted at the beginning of each month. During each session, videos recorded on the topic will be provided to the IG face-to-face, using smartphones, tablets, or handheld computers. Phone calls and SMS reminders will continue every week for follow-up and question-and-answer sessions. SDT will be employed for symptom management, maintaining and enhancing relationships, problem-solving, stress and coping, self-care, and effective communication. According to SDT principles, the symptom management component will provide education and resources to caregivers about symptom identification, monitoring, and management strategies appropriate for the specific needs of cancer patients, promoting the importance of social connections and supportive relationships to maintain and improve the care recipient and caregiver relationship. Caregivers will receive problem-solving skills training to identify and evaluate potential solutions, implement effective problem-solving strategies, and adjust their approach based on feedback and results. The intervention will provide educational materials and stress reduction techniques to help caregivers manage stress and improve their well-being. It means caregivers learn about how stress affects their bodies and minds and then practice various coping strategies to deal with the challenges of their caregiving role, promoting self-care practices to prioritize their own physical, emotional, and spiritual needs through activities such as exercising, relaxing, recreating, and self-reflection. The intervention included skills training to improve caregiver-patient communication and facilitate shared decision-making as part of effective communication based on self-determination theory. Definitions, benefits, and instructions regarding the BRT, such as diaphragmatic breathing, progressive muscle relaxation, and visualization exercises, will be provided through recorded videos. A nurse will guide the individuals face-to-face, after receiving training from a physiotherapist. Table 1 shows the intervention activities.

**Table 1 TAB1:** Study activities BRT: Benson relaxation technique; SMS: short messaging services

Schedule	Intervention group	Control group
First month	First week: We will provide videos on information on cancer, symptom management, and the BRT with individual face-to-face training on the BRT by a trained nurse who will receive training from a physiotherapist. Second, third, and fourth weeks: Phone call and SMS reminder (once a week) for follow-up and a question-and-answer session.	Usual care
Second month	First week: We will provide a video on maintaining and enhancing relationships. Second, third, and fourth weeks: Phone call and SMS reminder (once a week) for follow-up and a question-and-answer session.	Usual care
Third month	First week: We will provide a video on problem-solving. Second, third, and fourth weeks: Phone call and SMS reminder (once a week) for follow-up and a question-and-answer session.	Usual care
Fourth month	First week: We will provide videos on stress and coping. Second, third, and fourth weeks: Phone call and SMS reminder (once a week) for follow-up and a question-and-answer session.	Usual care
Fifth month	First week: We will provide a video on self-care. Second, third, and fourth weeks: Phone call and SMS reminder (once a week) for follow-up and a question-and-answer session.	Usual care
Sixth month	First week: We will provide a video on effective communication. Second, third, and fourth weeks: Phone call and SMS reminder (once a week) for follow-up and a question-and-answer session.	Usual care

Endpoints

The primary outcome involves assessing the change scores obtained from the ZBI. Meanwhile, the secondary outcomes are as follows: (1) assessment of changes in anxiety and depression levels by the HADS and (2) changes in QOL, as measured by the WHOQOL questionnaire. Both primary and secondary outcomes will be assessed at baseline, midline, and endline in both the IG and CG.

Measurements

ZBI

As a measure of caregiver burden, we will use the ZBI, which consists of 22 items [22]. The frequency of experiencing certain caregiver-related challenges is expressed on a Likert scale ranging from 0 to 4 as follows: 0=never, 1=rarely, 2=sometimes, 3=quite frequently, and 4=nearly always. Where higher scores represent a higher burden, the scores are the following: 0-21=little or no burden, 21-40=mild-to-moderate burden, 41-60=moderate-to-severe burden, and 61-88=severe burden.

HADS

The HADS will be used to evaluate the anxiety and depression levels [24]. Among the 14 items on a scale from 0 to 3, higher scores indicate anxiety or depression and the severity of their experience. Anxiety and depressive symptoms will be categorized according to predetermined criteria as follows: 0-7=normal levels, 8-10=borderline abnormal levels, and 11-21=abnormal levels.

WHOQOL-BREF

The WHOQOL-BREF will be used to assess the caregiver's QOL [25]. This instrument is particularly designed to evaluate multiple QOL components, including social interactions, environmental variables, psychological well-being, and physical health. A total of 26 items will rate their experiences on a Likert scale ranging from 1 to 5.

Data safety monitoring plan

Participants in this study have no minimal risk, and the researcher will treat all their personal information, including names, phone numbers, and addresses, as confidential and keep them secure. Confidentiality procedures will be implemented to ensure that participants' information is kept secure. Only members of our survey research team will have access to the data obtained from the questionnaires.

Statistical analysis

The IBM SPSS Statistics for Windows, Version 25.0 (Released 2017; IBM Corp., Armonk, New York, United States) will be used to evaluate the data. The results of the IG and CG will be compared using an intention-to-treat analysis. Continuous data will be presented as mean and standard deviation (SD), while categorical data will be represented as frequencies and percentages. Baseline data will be analyzed using various statistical tests, such as the chi-squared test, t-test, Mann-Whitney U test, Pearson's X2 test, or Fisher's exact test, to compare the two groups (IG and CG). A specific test will be employed depending on the variable type and distribution of the data. The mean values of the ZBI, HADS, and WHOQOL-BREF will be compared between the two groups at baseline, midline, and endline to assess the efficacy of the intervention. Comparisons will be performed using independent t-tests. Additionally, two-way repeated-measures analysis of variance (ANOVA) will be employed to evaluate changes in outcomes over time within each group (from baseline to endline). This analysis considers the IG, time, and their interactions. Statistical significance will be set at p<0.05. The latest observation carried forward approach will be applied to data imputation to resolve missing data.

Ethical considerations

The principles of the Declaration of Helsinki will be followed while conducting the study [27]. We obtained ethical approval from the Ethical Review Committee (ERC) of the Department of Public Health, Northern University Bangladesh (NUB) (approval number: NUB/DPH/EC/2023/26), and the clinical trial has been registered on ClinicalTrials.gov under the clinical trial registration number NCT06204328.

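### The exclusion of caregivers for traumatic events during the study, including the patient's death, conflicts with the stated intention-to-treat analysis and can remove randomised caregivers for outcome-related reasons

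*Protocol article*

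**What the plan says.** Under Study participants, Eligibility Criteria, the list of exclusions contains "those experiencing extremely traumatic events that occurred during the study (such as the deaths of loved ones or patients, separations, etc". The same list contains "those who refused to collaborate with the ongoing study".

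The Randomization section states that "there will be a 1:1 open-label randomization for either the IG or the CG". Data Collection and Follow-Up sets the visits: "Data will be collected at baseline (before the intervention), midline (after three months of intervention), and endline (after six months of intervention". Under Endpoints, "The primary outcome involves assessing the change scores obtained from the ZBI"; anxiety and depression (HADS) and quality of life (WHOQOL-BREF) are secondary.

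The Statistical analysis section gives the population: "The results of the IG and CG will be compared using an intention-to-treat analysis". It also gives the missing-data rule: "The latest observation carried forward approach will be applied to data imputation to resolve missing data".

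**The concern.** An eligibility criterion should be decidable before allocation. This one depends on what happens during the study, so it works at least partly as a rule for removing people who have already been randomised. Intention-to-treat means the opposite: everyone randomised is analysed in the assigned arm.

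The removal would not be neutral. Bereavement and separation bear directly on anxiety, depression and quality of life, and a patient's death ends the caregiving that the ZBI measures. Allocation is known, and whether an event counts as extreme enough is a judgement, with an open-ended list of examples. Table 1 gives the intervention arm a weekly call in most weeks and the control arm usual care only, so events could come to notice more often in one arm. If removal differs by arm and is related to outcome, the comparison of those who remain is no longer protected by randomisation.

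**Working it through.** **1. The two rules applied to one case.** Take a caregiver who is randomised and interviewed at baseline and midline, and whose patient dies in month four.
- Eligibility Criteria: she meets an exclusion criterion.
- Statistical analysis: she stays in her arm, and if her endline is missing, her midline value is carried forward.

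The article does not say which applies, or whether exclusion means removal from the analysis or only the end of follow-up.

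**2. Timing.** The Results section has enrolment from January 2024 and the intervention expected in April 2024, and the Eligibility Criteria describe a baseline survey before enrolment. Some events during the study could therefore precede allocation. The intervention and follow-up then run six months, so most of the period covered by the rule lies after allocation.

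**3. What removal could do to the comparison.** Suppose the intervention has no effect and both arms have the same overall mean, set to 0. Let a fraction e of an arm be removed, and let those removed score k SD above those retained. Then e(m + k) + (1 − e)m = 0, so the retained mean is m = −e·k. The spurious difference, intervention minus control, is k(e_C − e_I).

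| Removed, intervention | Removed, control | k | Spurious difference (SD) |
|---|---|---|---|
| 10% | 10% | 1 or −1 | 0 |
| 10% | 20% | 1 | 0.2 − 0.1 = +0.10 |
| 10% | 20% | −1 | −0.10 |
| 5% | 20% | 1 | 0.20 − 0.05 = +0.15 |

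The rates and k are assumptions. The table shows that the bias vanishes with equal removal when k is the same in both arms, and that its sign follows k, which the documents do not give. For scale, 0.10 SD is 0.10/0.72 = 14% of the design effect.

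**4. The plan's own sample size.** Inputs from Sample Size: d = 0.72, confidence level 0.95, power 0.90, two independent means. For n per arm, the noncentrality is d·√(n/2) on 2n − 2 degrees of freedom. A two-sided t-test at 0.05 needs n = 41.52, so 42 per arm and 84 in total, matching the article. A one-sided test would need 34 per arm, or 68, which does not match, so two-sided is used below.

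**5. Power under assumed losses from 51 per arm.**

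| Case | n per arm | 0.72·√(n/2) | Power |
|---|---|---|---|
| No loss | 51 | 3.64 | 0.950 |
| Events within the planned 20% dropout | 51 × 0.8 = 40.8 | 3.25 | 0.895 |
| A further 10% on top | 51 × 0.8 × 0.9 = 36.7 | 3.09 | 0.861 |
| A further 20% on top | 51 × 0.8 × 0.8 = 32.6 | 2.91 | 0.817 |

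**The case against.** The best defence is that exclusion here means only that follow-up stops. The caregiver would stay in her arm with her last value carried forward, the randomised set would be intact, and the rules would not collide. This reading is possible, so it would be too strong to say that the two rules can never be followed together. But the article does not state it, and the clause sits among the exclusion criteria. It also brings its own difficulty: the primary outcome is a change score, so a caregiver whose patient dies before midline would carry her baseline forward and be scored as unchanged, although the caregiving has ended.

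It can also be said that a journal article condenses the protocol and that a separate analysis plan may exist. That would answer a complaint about missing detail. It does not answer a stated criterion that conflicts with a stated analysis population.

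Four stronger readings are tempting, and the documents do not support them:
- **That the most burdened caregivers are removed.** After a patient's death the ZBI could rise, fall or cease to apply.
- **That patient deaths will be common and a main source of attrition.** The Discussion says only that stage will vary. Deaths are foreseeable, since the criterion names them, but no rate is given.
- **That the refusal criterion is a second post-randomisation exclusion that differs by arm.** It reads most naturally as declining at enrolment.
- **That the trial will be underpowered.** The dropout allowance may already cover these losses.

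**Conclusion.** The point holds as a conflict between two stated rules. The criterion excludes caregivers for events during the study, most of which would fall after allocation, while the analysis is described as intention-to-treat. If the criterion is applied as written, randomised caregivers are removed for outcome-related events in an open-label trial.

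The consequence is a possible selection bias of unknown size and direction. It rests on two assumptions: that exclusion means removal from the analysis, and that removal differs between arms in its rate or in who is removed. Power is secondary. It is 0.895 against the planned 0.90 if the losses fall within the 20% allowance, and lower only if they are additional.

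**What to change.** Reconcile the Eligibility Criteria with the Statistical analysis section:

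1. Limit the traumatic-event exclusion to events known before randomisation.
2. State that every randomised caregiver stays in the analysis in the assigned arm.
3. After a patient's death or a separation, continue HADS and WHOQOL-BREF collection where the caregiver agrees.
4. Do not carry a ZBI score from before a death forward by default without a sensitivity analysis.
5. Report the number of such events by arm.
6. Reword the refusal criterion to say that it means refusal at enrolment.

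The cost is a wording amendment, a few interviews that would otherwise be dropped, and one added sensitivity analysis. The planned total stays at 102. The planned t-tests and repeated-measures ANOVA need not be replaced to resolve this point.

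### The dropout allowance multiplies by 1.2 instead of dividing by 0.8, so 102 enrolled with 20% dropout leave 81 or 82 completers rather than the required 84 (a minor slip)

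*Protocol article*

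**What the plan says.** All the planning figures stand in the protocol article, Materials and methods, under Sample Size.

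- Effect size: "An effect size of 0.72 was estimated based on a similar previous study".
- Error rate and power: "a confidence level of 0.95, and a statistical power of 0.90", for a comparison of two independent means. Sidedness is not stated.
- Result: "The sample size required for the study was 84 caregivers".
- Allowance for losses: "Eighteen additional caregivers will be recruited to compensate for potential dropouts".
- Total: "Following a 20% dropout rate, the total number of participants was 102", divided equally as 51 per arm.

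The Statistical analysis section adds that the groups are compared by intention to treat and that missing data are filled by carrying the last observation forward.

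**The concern.** An allowance for dropout should return the required number once the assumed losses have occurred. Here it does not: at the plan's own 20%, fewer than 84 of the 102 remain. The required number, the dropout rate and the total are the planning figures that a trial report will repeat, and they should agree with one another. What is at stake is mainly the accuracy of that statement. There is also a small amount of power, if the number of completers is taken as the effective sample size.

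**Working it through.** **Inputs** (Sample Size section): standardised difference d = 0.72; alpha 0.05, from the confidence level of 0.95; target power 0.90; equal arms; 84 required; 18 added; 102 in total; 20% dropout. A two-sided test is my assumption.

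**Step 1: reproduce 84.** Exact power of the two-sample t-test uses the noncentral t distribution with df = n1 + n2 − 2 and noncentrality d × √(n1·n2/(n1 + n2)).

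- Two-sided, 42 per arm: 0.72 × √21 = 3.30, df = 82, power 0.9033. With 41 per arm, power is 0.8963. So 42 per arm, 84 in total, is the smallest equal-arm size that reaches 0.90. The plan's figure is reproduced.
- One-sided, the same method needs 34 per arm, 68 in total.
- The two-sided normal approximation gives 41 per arm, 82 in total.

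Of these, only the two-sided exact test gives 84, which supports the assumption.

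**Step 2: reproduce 102.**

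- Multiplying: 42 × 1.2 = 50.4, rounded up to 51 per arm, 102 in total. The addition is 9 per arm, 18 in all.
- Dividing: 84 / (1 − 0.20) = 105. With equal arms, 42 / 0.80 = 52.5, rounded up to 53 per arm, 106 in total.

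The article does not show the step, but multiplication followed by rounding within arms gives both the 18 and the 102 exactly.

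**Step 3: apply the stated dropout.**

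- 102 × 0.80 = 81.6 completers, so 81 or 82, which is 3 or 2 fewer than 84.
- The largest loss from 102 that still leaves 84 is 18/102 = 17.6%.
- Check of the alternatives: 105 × 0.80 = 84.0; 106 × 0.80 = 84.8.

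**Step 4: power at d = 0.72, two-sided 0.05.**

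| Analysed (per arm) | Power |
|---|---|
| 84 (42/42) | 90.3% |
| 82 (41/41) | 89.6% |
| 81 (41/40) | 89.3% |
| 102 (51/51), effect undiluted | 95.0% |

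Against the 90% target, the shortfall with 82 or 81 completers is 0.4 or 0.7 percentage points.

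**Step 5: what carrying observations forward could do.** The documents do not say when dropouts leave, so this is a range and not an estimate. If dropouts carried the full effect, all 102 would count and power would be 95.0%. If instead 20% in each arm left before midline, their baseline values were carried forward and the SD did not change, the effect would shrink to 0.72 × 0.80 = 0.576. Power with 102 would then be about 82%. The stated 90% lies inside this range.

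**The case against.** The strongest reply is that nothing of substance is lost. The power gap is under one percentage point, and d = 0.72 comes from a single previous study, so uncertainty about the effect size matters more than two or three participants. This stands, and it makes the point minor.

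A second reply is that the planned analysis is not a completer analysis. Participants who drop out stay in by having their last observation carried forward, so the nominal size is 102. This also stands as far as it goes. A reader might infer from the 81 to 82 completers that the stated 90% power is not met, but the documents do not support that: the completer figures describe an analysis that the plan does not use. The reply does not remove the slip, though. The Sample Size section adds 18 people expressly to make up for dropouts, so its own logic treats them as lost, and on that logic the allowance should return 84. Nor does carrying observations forward guarantee the power, since the carried values may dilute the effect.

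A third reply is that the 18 is not arbitrary. It is 20% of the required number, rounded up within each arm (8.4 to 9). That is right, and a reader who takes 18 to be an unexplained number would be wrong. The fault lies in the convention: a dropout rate is a proportion of those enrolled, not of those required to finish.

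A reader might also infer that there is no room for caregivers lost because the patient dies, since traumatic events during the study are listed among the exclusions. The article does not define what the 20% covers, and it may include such losses.

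**Conclusion.** The point holds as a minor arithmetic inconsistency. With 20% dropout, 102 enrolled leave 81 or 82 completers, 2 to 3 short of the stated 84. The total that satisfies both figures is 105, or 106 with equal arms. On a completer basis, power is about 89.3% to 89.6% instead of at least 90%. This rests on a two-sided 0.05 t-test, on d = 0.72 and on losses spread about evenly over the arms. It does not show that the trial is underpowered. The base figure of 84 is correct under the two-sided assumption; only the inflation step is at fault.

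**What to change.** Restate the figure in the Sample Size section in one of two ways:

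- 102 participants (51 per arm) allow for about 17.6% dropout while leaving 84; or
- with 20% dropout, about 82 completers remain and give about 89% to 90% power at d = 0.72, two-sided 0.05.

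Either way, add that the test is two-sided. The cost is one sentence, with no change to enrolment, design or analysis; the stated figure becomes slightly less favourable. Only if 20% dropout and 84 completers must both stand does the total need to rise to 105, or to 106 (53 per arm) for equal arms: three or four more caregivers. The size of the gap does not by itself call for that.
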